## 3. Discussion

Previous studies on acupuncture for the treatment of COPD demonstrate that acupuncture can result in important clinical improvements in quality of life and dyspnea [21,44]. However, existing studies provide insufficient evidence due to methodological limitations, including poor study design, inadequate control groups, and variations in AT. A systematic review on the topic published in 2018 showed that the methodological quality of the included studies was generally low. For example, most of the included studies were at high risk of performance bias. In addition, most analyses of the data in the meta-analysis indicated heterogeneity across studies. Finally, there were several forms of intervention adjunct to acupuncture, which makes it difficult to assess the effectiveness of acupuncture alone [45].

Therefore, more rigorously designed studies are needed to elucidate the efficacy of acupuncture therapy for the treatment of patients with COPD and its response in regard to HRQoL (primary outcome). Moreover, there is also a need to analyze functional performance limited by dyspnea in ADLs, the impact of COPD on patients’ lives, and these patients’ pulmonary function (secondary outcomes). We therefore propose a randomized clinical trial with the evaluators blinded in addition to blinding the researcher to patient allocation. The data will be coded in a nonidentifiable way and will not contain any information that could indicate bias regarding patient allocation. The study will have a 16-week follow-up, with reapplication of tests and questionnaires at 8 weeks, enabling assessment of the responses in the short and long term, which, according to our previous review, has not yet been performed. In addition, our control group will not undergo any intervention, thereby providing analysis of the isolated effect of acupuncture on patients with COPD.

Control procedures involving invasive or noninvasive sham needling techniques can be therapeutically active, evoking localized neurophysiological and/or immune and circulatory responses [46,47,48,49]. There are also variations in assumptions about the accuracy needed for point location, as some acupuncturists and researchers consider acupuncture points areas of reactivity rather than action points. These assumptions affect the integrity of sham acupuncture as an appropriate control [28].

The PEDro (Physiotherapy Evidence Database) provides easy access to high-quality clinical research by physical therapists around the world, enabling the application of evidence in practice and effective teaching. All randomized clinical trials indexed in the PEDro are classified and can receive a maximum score of 10 points, according to their quality through the PEDro scale. This classification enables readers to identify relevant and valid studies to guide them in clinical practice [50].

A bibliographic survey using the PEDro database shows only one study that evaluated the effect of AT on the quality of life of patients with COPD with a score of 8; the other studies had scores of 5 or less, that is, were of low methodological quality according to the database. Although Feng’s 2016 study obtained a score of 8 in terms of methodological quality, gaps remain regarding the isolated effects of acupuncture, as the study used a sham group as a comparator [22]. The use of sham acupuncture using the application of the needle at points other than those of oriental medicine or the use of seeds in place of the needle or even the use of a placebo needle can generate interpretation bias considering the mechanical effects and the pressure exerted on the biological tissue. Given the consideration that sham acupuncture can be as effective as traditional acupuncture [46,47,48,49], there remains a gap regarding the isolated effects of acupuncture. Furthermore, in addition to HRQoL, secondary outcomes such as functional performance, functional limitations, dyspnea in activities of daily living, and the impact of the disease on life are crucial for the global understanding of the effectiveness of acupuncture in patients with COPD. Therefore, conducting the present study is justified in terms of relevance and practical potential for application.

Our work predicts a score of 8 on the PEDro scale as we plan to specify eligibility criteria, randomly assign patients, and use veiled subject allocation by a researcher designated exclusively for this role during research planning, performed using a computer program; we will have well-defined inclusion and exclusion criteria ensuring similar groups with regard to the most important prognostic indicators at baseline; and there will be blinding of the evaluators who will measure the outcomes. Furthermore, we will aim to ensure patient adherence, ensuring that measurements of at least one key outcome will be obtained in more than 85% of subjects initially distributed among the groups, using weekly telephone calls made to patients in the control group; data will be analyzed by intent to treat; we will describe the results of intergroup statistical comparisons in at least one key result; and we will describe measures of precision as measures of variability for at least one key outcome. We will lose in points that do not apply to studies with acupuncture, i.e., blinding of subjects and blinding of the therapist who will apply the therapy. In addition, we will follow up for a total of 16 weeks by reapplying the tests and questionnaires at 8 weeks, which will enable assessment of the responses in the short and long term, which, according to our previous review, has not yet been undertaken.

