## 2. Materials and Methods

### 2.1. Design

The study will be a two-arm, parallel-group, prospective, computer-randomized, controlled, evaluator-blind design lasting for 16 weeks (two eight-week intervention periods). The study was registered on the www.ensaiosclinicos.gov.br (accessed on 23 May 2022) (REBEC) website. The protocol has been developed according to the SPIRIT guidelines [26] and described according to the CONSORT statements [27]. The acupuncture protocol will follow the recommendations of the Standards for Reporting Interventions in Clinical Trials of Acupuncture (STRICTA), a formal extension of CONSORT. STRICTA was designed to improve the integrity and transparency of reporting interventions in clinical trials of acupuncture so that such trials can be more accurately interpreted and easily replicated [28]. Furthermore, the intervention will be reported according to the Model for Intervention Description and Replication (TIDieR) checklist and guide [29].

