### 2.2. Patients

Patients with a clinical diagnosis of COPD who meet the inclusion criteria will be recruited from the waiting list of the Federal University of the Jequitinhonha and Mucuri Valleys (UFVJM) Physiotherapy school clinic, as well as in doctors’ offices and hospitals and through pamphlets and advertisements on local radio.

Patients will be aware that they will be randomized into one of two groups. Group I will receive AT and Group II will be without AT–we chose a control group without any intervention in order to analyze the isolated effect of AT. At the end of the project, if the results are favorable, patients in the control group will be offered the possibility of receiving AT.

The sample size was estimated using the GPower^®^ program (Franz Faul, Universitat Kiel, Kiel, Germany), version 3.1.9.2. For this, a priori analysis was used, considering the t-test for comparisons between groups, for the quality-of-life variable evaluated by the Saint George Respiratory Questionnaire (SGRQ)-Total score [22]. Thus, considering an effect size of 0.59 [22], power of 0.80%, and alpha error of 5%, the sample size was estimated at 50 patients for each group, totaling 100 patients. These calculations assumed a 20% loss in the worst-case scenario.

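### A no-acupuncture control with unblinded patients and self-reported primary outcomes gives the total effect of a course of acupuncture, not an 'isolated' effect that a sham-controlled trial could not show

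*Protocol article*

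**What the plan says.** Section 2.2 (Patients) gives the reason for the control: "we chose a control group without any intervention in order to analyze the isolated effect of AT". Section 3 (Discussion) repeats it as a consequence of the design: "our control group will not undergo any intervention, thereby providing analysis of the isolated effect of acupuncture on patients with COPD".

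Further on, the Discussion considers the one earlier trial that it rates highly. It holds that the isolated effect remains unknown after that trial because the comparator was sham, and it supports this with "Given the consideration that sham acupuncture can be as effective as traditional acupuncture".

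On blinding, section 2.1 (Design) claims blinding of the evaluator only. The Discussion lists among the PEDro points that the trial will forgo "blinding of subjects and blinding of the therapist who will apply the therapy". Section 2.6 (Outcome Measures) makes SGRQ and PGI the primary outcome.

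On contact, the Abstract sets AT at three times a week for eight weeks and then continues it for eight more. Control patients are to be kept in the study "using weekly telephone calls made to patients in the control group".

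**The concern.** To say that a contrast isolates an effect is to say what it identifies. A difference between arms identifies needling alone only if the arms are alike in everything else that can move the outcome. Here they also differ in what patients expect, in time spent with a therapist, and in patients' knowledge of their group when they fill in the questionnaires.

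At stake is the conclusion. A positive result could be reported as the effect of acupuncture itself, and as closing a gap left by sham-controlled research. The question that the trial can answer is useful but different: does a course of AT improve reported quality of life compared with no AT?

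**Working it through.** The plan gives no figure for this point, so the check sets its statements side by side and then adds two pieces of arithmetic.

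**1. Who assesses the primary outcome.** In the PGI (section 2.6.1) the patient names the affected areas, rates them and allocates the tokens. The SGRQ total is built from the patient's own answers. The patient is in effect the assessor and is not blinded. Evaluator blinding can protect how a test is conducted or scored, but not what an unblinded patient reports.

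**2. What differs between the arms.**
- AT arm: 3 sessions/week × (8 + 8) weeks = 48 sessions. Under Acupuncture in section 2.5, needles stay in for 30 min after the last insertion, so contact is at least 48 × 30 min = 1,440 min = 24 h.
- Control arm: 1 call/week × 16 weeks = 16 calls, assuming that the calls run throughout. Their length is not stated.

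**3. What the difference contains.** AT minus control = needling + expectation + contact + unblinded reporting. The design has nothing that separates these terms. Randomisation removes natural history and baseline differences, and the absence of adjunct therapy removes co-interventions. Neither removes the last three terms.

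**4. Two meanings of 'isolated'.**
- Introduction, and the part of the Discussion on adjunct interventions: AT alone, as opposed to AT added to or compared with another therapy. A randomised no-AT control supports this.
- The part of the Discussion on the sham-controlled trial: something that a sham comparison fails to show. Replacing sham with no treatment adds components to the difference; it does not remove any.

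**5. Illustration on assumed values.** Suppose that needling has no effect and the other components shift SGRQ total by *b* SD. For a two-sided 5% t-test with *n* per arm, the noncentrality is *b* × √(n/2), which is 5*b* for n = 50 and 4.47*b* for n = 40 (50 less the plan's 20% loss). The chance of p < 0.05 is:

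| assumed *b* | n = 50 | n = 40 |
|---|---|---|
| 0.1 | 8% | 7% |
| 0.2 | 17% | 14% |
| 0.3 | 32% | 26% |
| 0.4 | 51% | 42% |
| 0.5 | 70% | 60% |
| 0.59 | 83% | 74% |

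The last row uses the plan's own design effect size for scale. The other values of *b* are assumptions; the documents contain no estimate. The t-test is the one named for the sample size, not the planned mixed model.

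**The case against.** The best defence is that the protocol explains its term. The Introduction sets the isolated effect against additive and comparative studies, and the Discussion complains of interventions given alongside acupuncture. In that sense the design delivers. The stated aim (Abstract) and hypothesis (Introduction) do not use the word at all. This stands, and it limits the point to sections 2.2 and 3. It does not cover the argument about the sham-controlled trial, where the absence of adjunct therapy is not what is in dispute.

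A second defence is that the lack of blinding is disclosed. It is, but as lost points on a quality scale. The article does not draw the consequence for SGRQ and PGI, although its Discussion faults earlier trials for high risk of performance bias.

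Some stronger readings are tempting, and the documents do not support them:

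- *The comparison isolates nothing.* A reader might infer this, but the comparison does separate AT from co-interventions and, through randomisation, from natural history.
- *The calls contradict a control without intervention.* The Discussion presents them as a means of retention and of obtaining outcome data, not as treatment. Calling only patients who do not attend three times a week also narrows the contact gap slightly. This is a matter of accurate description.
- *The premise that sham may match real acupuncture shows that the benefit would be expectation.* The protocol attributes sham activity to physical effects of needle or pressure, and it does not expressly claim point specificity. What remains is that, on its own premise, a difference from no treatment would say nothing about the chosen points.
- *The trial needs a sham arm.* The protocol's concern that sham is active is a legitimate reason to avoid it, and the comparison with no AT answers a question of its own.

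**Conclusion.** The point holds in limited form. Sections 2.2 and 3 state or imply a property that the design lacks: an effect of acupuncture separated from expectation, contact and unblinded reporting, which a sham-controlled trial could not supply. The trial estimates the total effect of a course of AT versus no AT in patients who know their group. The narrower sense, AT without adjunct therapy, is sound.

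This rests on what the article states about blinding, outcomes and contact (48 sessions against about 16 calls), and not on any assumed bias. The size of the non-needling part cannot be derived from the documents. The illustration shows only that a moderate shift, if present, would often be enough for significance. Sample size, primary outcome and analysis need not change on this account, but what may be concluded does.

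**What to change.** - **Sections 2.2 and 3:** define the contrast as the *effect of a course of AT given without adjunct therapy, including contact and expectation, versus no AT (with weekly retention calls), in patients aware of their group*.
- **Discussion of the sham-controlled trial:** drop the implication that this trial closes the gap which that trial left. The Introduction's use of the term can stay.
- **Interpretation:** state that no needle- or point-specific conclusion will be drawn, and that evaluator blinding does not protect SGRQ or PGI from unblinded reporting.
- **Reporting:** interpret the primary result beside spirometry, which is already planned after Phases II and III and is less subjective. It gives context only: it still depends on effort, and no change in lung function would not refute a change in quality of life.
- **Optional:** ask the same structured weekly questions in both arms, at an existing visit in the AT arm and by the existing call in the control arm.

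The cost is a few sentences and, if the option is taken, one short weekly set of questions. The downside is a more modest claim.

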## Figures and Tables

**Figure 1 jcm-11-03048-f001:**
[figure not shown]
Flow of participants throughout in all stages of the research.

## Data Availability

The data presented in this study are available on request from the corresponding author. The data are not publicly available due to the privacy guarantee of the data collected individually.
